### Sample Size Calculation

In this study, the disappearance time of cough is used as the primary outcome. According to previous studies, the disappearance time of cough in the experimental group and the control group is about 5 ± 2 days. The non-inferiority threshold of this study is set as 0.5 days, unilateral α = 0.025, power = 0.95, and the PASS (V14.0) is selected to estimate the sample size. Based on the calculation, 417 cases are needed for each group. After considering the proportion of withdrawals, the sample size of this study is 500 cases for each group, with a total of 1000 cases.

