### Intervention Method

The Intervention group takes JZOL and AHCHOS placebo, while the control group receives AHCHOS and JZOL placebo. Both drugs and their placebos are taken orally. According to different ages and weights, the dosages of the two drugs are shown in Table 1. The conditions treated by the two drugs in this study are the same as publicly available information. Ibuprofen Suspension will be taken when two groups of participants appear in an emergency. The medication lasts for 7 days. The treatment medicine and their placebos are provided by Jiangsu Kanion Pharmaceutical Co., Ltd according to the double-blind principle. The schedule of enrollment, interventions, and assessments is shown in Table 2.

**TABLE 1 T1:** Usage instructions for both drugs.

Jinzhen oral liquid and its placebo		
**Age**	**Dosage**	
2–3 years old	10 ml each time, twice a day	
4–7 years old	10 ml each time, three times a day	
8–14 years old	15 ml each time, three times a day	
Ambroxol Hydrochloride and Clenbuterol Hydrochloride Oral Solution and its placebo		
** Age**	**Weight**	**Dosage**
** 2–3 years old**	12–16 kg	7.5 ml each time, twice a day
** 4–5 years old**	16–22 kg	10 ml each time, twice a day
** 6–12 years old**	22–35 kg	15 ml each time, twice a day
** More than 12 years old**	—	20 ml each time, twice a day

Note: In case of inconsistency between age and weight, the dosage can be adjusted according to their weight.

**TABLE 2 T2:** Flow chart for clinical trial.

Stage procedure	Screening stage /Baseline (1st Visit)	During treatment (2nd Visit)<	After treatment (3rd Visit)
	−1 ∼ 0 days	5 ± 1 day	7 ± 1 day
Patient screening	×	—	—
Sign informed consent form	×	—	—
Fill in demographic information	×	—	—
Past medical history	×	—	—
Medical comorbidities and current medication	×	—	—
Chest radiograph	×	—	—
General examination	×	×	×
Physical examination	×	×	×
TCM syndrome scoring and grading	×	×	×
Routine blood investigations, urinalysis and stool examination	×	—	×
Liver function tests (ALT, ALP, AST, TBIl, γ-GT) and kidney function tests (BUN, Cr)	×	—	×
ECG	×	—	×
Stool/salivary metagenomic analysis	×	×	×
Stool/blood metabolomics analysis	×	×	×
Distribution and withdrawal of the remaining intervention medication	×	—	×
Distribution and withdrawal of patients’ medication diary record cards	×	×	×
Adverse events record	—	×	×
Combination therapy medication record	—	×	×
Conclusion (Trial Summary)	—	—	×

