#### Outcome Evaluation

##### Primary Outcome

The disappearance time of cough should be recorded daily, then evaluated at the study endpoint.

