##### Secondary Outcome

(1) Area Under Curve (AUC) of cough and expectoration symptom score-time, cough symptom score (Table 3), antitussive onset time, clinical recovery time, and TCM syndrome score (Li, 2015) (Table 4) will be daily recorded and evaluated at the study endpoint.i. Cough disappeared: cough symptom score (daytime + night) ≤1 point, and maintained for 24 h or more.ii. Antitussive onset time: the number of days required for cough symptom score to decrease by one point after taking the medicine.iii. Clinical recovery: cough, expectoration and pulmonary symptoms are all mild after treatment, without affecting study, living and sleep.iv. Evaluation criteria for the efficacy of TCM syndromesA. Clinical recovery: the total score decreased by ≥90%.B. Significant effect: the total score decreased by ≥70% and <90%.C. Effective: the total score decreased by ≥30% and <70%.D. Ineffective: those who fail to meet the above standards.(2) The disappearance rate of cough, sputum and pulmonary rales will be evaluated at the study endpoint.(3) The usage of antibiotics, antipyretics or analgesics will be evaluated at the study endpoint.

**TABLE 3 T3:** Cough symptom scoring.

Score	Daytime symptom	Night symptom
0	No cough	No cough
1	Short occasional cough	Short occasional cough during sleep
2	Frequent cough, daily activities mildly affected	Slight disturbance of sleep due to cough
3	Frequent cough, daily activities severely affected	Severe disturbance of sleep due to cough

**TABLE 4 T4:** Quantitative Grading evaluation for TCM syndrome.

Grading symptoms		(−)	(+)	(++)	(+++)
Primary symptoms		0	1	2	3
Cough	Daytime	No cough	Short occasional cough	Frequent cough, daily activities mildly affected	Frequent cough, daily activities severely affected
	Night	No cough	Short occasional cough during sleep	Slight disturbance of sleep due to cough	Severe disturbance of sleep due to cough
Expectoration	Daytime	No expectoration	Phlegm is whitish and slightly sticky	Phlegm is whitish/yellowish and sticky	Phlegm is yellowish and sticky
	Night	No expectoration	Phlegm is easy to cough out	Phlegm is slightly difficult to cough out	Phlegm is difficult to cough out
Secondary Symptoms		0	1	2	3
Fever (24 h maximum axillary temperature)		≤37.2°C	37.3–37.9°C	38.0–38.5°C	>38.5°C
Thirsty		No	Yes	Yes	Yes
Facial Erythema		No	Yes	Yes	Yes
Dysphoria		No	Yes	Yes	Yes
Scanty dark-colored urine		No	Yes	Yes	Yes
Dry stool		No	Yes	Yes	Yes
Tongue and pulse condition		Normal	Abnormal	Others	

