### Statistical Analysis

SAS will be used for statistical analysis. Intention-to-treat analysis will be carried out in this trial, which refers to the analysis of all cases that have been randomized and used drugs at least once. All statistical tests are conducted using a two-sided test, and *p* <0.05 would be considered statistically significant. The missing data will be filled up by carrying forward the last measured value in this trial. Covariance analysis is used for the evaluation of the cough disappearance time. The group is taken as a fixed effect, and the baseline value of the cough symptom score is taken as covariance into the model for analysis. The difference between the different values of the two groups and their bilateral 95% confidence intervals are calculated. Then, the lower limit of bilateral 95% confidence intervals and the preset non-inferiority standard are compared to determine whether the test group is inferior to the control group. In addition, the subgroup analysis is performed according to age (2–3 years, 4–7 years, and 8–14 years). Measurement methods and data sets of secondary outcomes are shown in Table 5. In terms of safety, the number of AEs and SAEs during the study will be listed, and their incidence will be calculated.

**TABLE 5 T5:** Secondary outcome.

Secondary outcome	Test method	Data set
Time-lapse analysis of measured value and changed value of cough symptom score	T test is used to compare the differences between groups	FAS^a^
AUC of cough and expectoration symptom score - time		
Onset of cough relief		
Clinical recovery time		
Disappearance rate of cough, expectoration and lung rales	χ2 test or Fisher’s exact probability method is used to compare the differences between groups	
Use of antibiotics, antipyretics and analgesics		
Analysis on the curative effect of TCM syndrome	CMH chi-square is used to compare the differences between groups	

a FAS, Full Analysis Set; AUC, Area Under Curve.

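### ANCOVA is fixed for cough disappearance time although observation stops around day 7, so on the plan's own 5 ± 2 days about 16% of children have no observed time

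*Protocol article*

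**What the plan says.** The Primary Outcome section states: "The disappearance time of cough should be recorded daily, then evaluated at the study endpoint". The definition of disappearance appears under Secondary Outcome: "cough symptom score (daytime + night) ≤1 point, and maintained for 24 h or more". On exposure, Intervention Method states "The medication lasts for 7 days". Table 2 puts the third and last visit at day 7 ± 1 and shows no efficacy observation after it.

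Sample Size Calculation assumes that "the disappearance time of cough in the experimental group and the control group is about 5 ± 2 days". It then gives the design: "The non-inferiority threshold of this study is set as 0.5 days, unilateral α = 0.025, power = 0.95", leading to "417 cases are needed for each group" and 500 per group after allowance for withdrawals.

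Statistical Analysis fixes the model: "Covariance analysis is used for the evaluation of the cough disappearance time", with group as the fixed effect and baseline cough score as the covariate. The analysis set is every randomised child who took at least one dose. The only rule for absent values is last value carried forward. For onset of cough relief and clinical recovery time, Table 5 states: "T test is used to compare the differences between groups".

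**The concern.** A time to an event watched for about a week is right-censored. A child still coughing at the last visit has a time known only to exceed that day, and ANCOVA needs a number for every child. The carry-forward rule does not give one: carrying forward a cough score yields no time, and carrying forward the last day simply caps the time there. The 24-hour condition tightens this, because a low score first seen on the last diary day cannot be confirmed. The protocol itself expects unresolved children, since the rate of cough disappearance at the endpoint is a secondary outcome.

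This bears on the confirmatory claim. A non-inferiority test must guard against JZOL being truly slower. In that case more JZOL children than control children are cut off, and a cap at the end of observation removes more time from the JZOL arm. The difference shrinks towards zero, the standard deviation falls, and non-inferiority becomes easier to declare.

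**Working it through.** **Inputs from the protocol:** mean 5 and SD 2 days in both groups, margin 0.5 day, one-sided 0.025, power 0.95, 417 and 500 per group, last visit at day 6 to 8. **Assumptions:** normal times, no gain from the baseline covariate, 5 ± 2 and the margin both on the uncensored scale. Difference = JZOL minus control; non-inferiority is declared if the upper 95% limit is below 0.5.

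**1. The plan's own figure.** n = 2 × 2² × (1.960 + 1.645)² / 0.5² = 415.8, so 416. The noncentral t version gives 417 (power 0.9501). The stated 417 reproduces, and it presumes that every time is fully observed with SD 2.

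**2. Share with no observed time by day T.** 1 − Φ((T − 5)/2):
- T = 6: 1 − Φ(0.5) = 30.9%
- T = 7: 1 − Φ(1.0) = 15.9%, about 79 of 500
- T = 8: 1 − Φ(1.5) = 6.7%

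With the same mean and SD, gamma times give 15.4% and lognormal times 14.3% at day 7.

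**3. Unresolved children set to day 7, JZOL truly 0.5 day slower (mean 5.5).** E[min(X,T)] = μΦ(a) − σφ(a) + T(1 − Φ(a)), with a = (T − μ)/σ.
- Control, a = 1: 5(0.8413) − 2(0.2420) + 7(0.1587) = 4.833
- JZOL, a = 0.75: 5.5(0.7734) − 2(0.3011) + 7(0.2266) = 5.238
- Difference 0.404; capped SDs 1.733 and 1.622; SE = √((1.733² + 1.622²)/500) = 0.106
- P(non-inferiority) = Φ((0.5 − 0.404)/0.106 − 1.96) = Φ(−1.06) = 14.5%

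**4. Unresolved children left out at day 7.** E[X | X ≤ T] = μ − σφ(a)/Φ(a).
- Control 5 − 2(0.2420)/0.8413 = 4.425; JZOL 5.5 − 2(0.3011)/0.7734 = 4.721
- Difference 0.296; SE 0.108 on about 421 and 387 children
- P(non-inferiority) = Φ(−0.08) = 47%

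**5. Summary at a true difference of 0.5 day, 500 per group.**

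| Handling | Expected difference | One-sided error |
|---|---|---|
| All times observed | 0.50 | 2.5% |
| Set to day 7 | 0.40 | 14.5% |
| Set to day 8 | 0.46 | 5.5% |
| Left out at day 7 | 0.30 | 47% |
| Left out at day 8 | 0.37 | 21% |

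At 417 per group the day-7 errors are 12.8% (cap) and 40% (left out).

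**6. Other shapes, by simulation.** Gamma times shifted by 0.5 day give 14.7% for a day-7 cap. Gamma times stretched by 10%, also 0.5 day in the mean, give 33%.

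**7. Other true differences, day-7 cap.** At zero difference the mean difference stays at zero, but the SD drops from 2.0 to 1.73 and the chance of declaring non-inferiority goes from 0.977 to 0.995. If JZOL is 0.5 day faster, the capped difference is −0.43, so its advantage is understated.

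**8. A penalty value instead of a cap.** Assigning 9 days to children unresolved at day 7 gives an expected difference of 0.54 day and an error of 1.2%; assigning 14 days gives 0.88 day and an error near zero. At zero true difference the chance of declaring non-inferiority falls to 0.946 and 0.550.

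**The case against.** The strongest reply is that the error figures come from handling rules the article does not state. An analysis plan not shown here may say what value an unresolved child receives. That stands: 14.5% and 47% are consequences of particular choices, not properties of a written rule. It does not remove the point, because the article fixes both the model and the carry-forward rule, and the two together give unresolved children no valid value.

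Three stronger readings are tempting, and the documents do not support them.
- A reader might infer that any imputation or omission favours non-inferiority. Step 8 shows otherwise for a value well above the last day. Leaving out children withdrawn for worsening could also act either way if withdrawal differs by arm.
- A reader might take 47% as the plan's error rate. Dropping unresolved children would depart from the stated analysis set.
- A reader might quote a day-6 cap, which gives 51%. That needs every child to finish at day 6, whereas medication runs 7 days and the last visit is labelled as after treatment. Day 8 is as much within the window and gives 5.5%.

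The 5 ± 2 days also comes from previous studies that are not shown. If those stopped at the end of a short course, both the SD and the margin may already be on a capped scale, and the calculation above would not apply as it stands. The article does not say so.

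Finally, the Table 5 t tests raise the same issue but cannot be sized from the document. Onset needs only a one-point fall, so censoring there may be slight.

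**Conclusion.** The point holds in this form: the primary model treats a right-censored time as fully observed, and the planning values make the censoring material. About 16% of children would be unresolved at day 7, with a range of 7% to 31% over the visit window. If they are set to the last observation day, the one-sided error at the margin is about 14.5% for day 7 and 5.5% for day 8, against the stated 2.5%. The sizes rest on a normal shape (gamma and lognormal give similar shares), a true deficit of 0.5 day, and 5 ± 2 days and the margin referring to uncensored times. The documents do not support saying that the error rate is breached whatever rule is chosen. They do show that the stated method gives no valid value for these children, which should be settled before unblinding.

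**What to change.** Analyse the primary endpoint by a method that treats children without a confirmed disappearance as censored at their last diary day, adjusting for baseline cough score and age stratum. Either option would do:
- **Censored or interval-censored regression**, giving the difference in days against the 0.5-day margin. Prespecify the distribution and add a sensitivity analysis under a skewed one. This matters: a normal-based censored regression holds close to 2.5% under normal times, but simulated error was roughly 7% to 12% under gamma or lognormal times with JZOL 10% slower.
- **Restricted mean time to one fixed common day**, with the 0.5-day margin and the sample size re-justified on that scale.

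Show Kaplan-Meier curves. Replace the t tests for onset time and clinical recovery time with time-to-event methods. Keep the existing diary card to one common last day, late enough to confirm events on day 7.

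Cost: analysis wording, about one more diary day and a later card collection; no extra patients. Under normal times with censoring at day 7, the standard error at 500 per group rises from 2√(2/500) = 0.126 to about 0.128. Power at zero difference is then Φ(0.5/0.128 − 1.96), about 97%. At 417 evaluable the standard error is 0.128 × √(500/417) = 0.140 and power is about 94.6%, close to the planned 95%. The restricted-mean option carries the further work of re-justifying the margin.

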## Materials and Methods

### Study Design

This clinical trial is designed as a stratified, randomized, double-blind, parallel-controlled, multi-center clinical study. The sample size is 500 participants in the intervention group and the control group respectively, with a total of 1000 participants. The trial will be carried out in 10 hospitals in China: *1*) Dongzhimen Hospital Affiliated to Beijing University of Chinese Medicine, *2*) Beijing Children’s Hospital, Capital Medical University, *3*) Children’s Hospital of Soochow University, *4*) Children’s Hospital Affiliated to Shandong University, *5*) The Second Affiliated Hospital of Heilongjiang University of TCM, *6*) Beijing Hepingli Hospital, *7*) Guangzhou Women and Children’s Medical Centar, *8*) Children’s Hospital of Shanghai, *9*) The First Affliated Hospital of Henan University of TCM, *10*) Xuzhou Children’s Hospital. All of these hospitals are qualified and experienced to conduct clinical trials. All enrolled participants will sign an informed consent before randomization. The flow chart of the trial is shown in Figure 1. There are three main objectives of the study. The first aim is to evaluate the effect of JZOL on shortening the course of AB and improving the condition in children. The disappearance time of cough is adopted as the primary outcome. The second aim is to assess the safety of JZOL in the clinical setting. The incidence of adverse events (AEs), routine blood investigations, blood biochemistry investigations, urinalysis, electrocardiogram (ECG), and stool routine tests are the main indicators to evaluate safety. The third aim is to explore the mechanism of action of JZOL in the treatment of AB by feces/saliva metagenomic analysis and feces/blood metabolomics analysis. The protocol will be reported following the Standard Protocol Items for Clinical Trials with Traditional Chinese Medicine 2018: Recommendations, Explanation and Elaboration (SPIRIT-TCM Extension 2018) (Additional file 1) (Dai, et al., 2019).

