### Randomization and Blindness

In this protocol, the stratified block randomization method is adopted. Participants will be stratified according to age. The age stratification is divided into five categories, which are 2–3 years old, 4–5 years old, 6–7 years old, 8–12 years old, and more than 12 years old. SAS 9.4 is used to generate random numbers and corresponding treatment groups. Random numbers are assigned by a central random platform (DAS for IWRS), and competitively selected by each clinical subcenter. There are two copies of the random scheme, which were sealed and stored respectively in the sponsor and the designer of the study scheme.

The double-blind method is used in this trial. Participants, clinicians, and outcome evaluators will be blinded. A two-stage blind design also will be used in the study. In this design, the statistical analyst will not know the grouping of medications in the study. Thus, the statistical analyst also will be blinded. To ensure the quality of blinding, all drugs and placebo are required to be uniformly packaged, while guaranteeing that there is no difference between real drugs and placebo in shape, color, sizer, taste, and smell. Entrust a third party to randomly number the corresponding medicines according to the random coding table and paste them in a conspicuous position in the external packaging of the medicines. The researchers logged on to the designed central random platform to obtain the random numbers of participants, and the pharmacy administrators of each clinical unit distributed the corresponding medicines to the patients according to the random number, to ensure that both researchers and patients were blinded. All the outcome measures and statistical analysts were not involved in the implementation of the trial, nor did they know the study design and hypotheses. If the participants experience SAEs during this trial, the principal investigator at each center has the authority to log in to the central randomization platform to unblind the patients, the reason for urgent unblinding should be noted, dated, and recorded on case report form (CRF).

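### Age is a five-level randomisation stratum but is missing from the stated primary ANCOVA, so the non-inferiority interval is somewhat wider than it need be (conservative, not biased)

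*Protocol article*

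**What the plan says.** Protocol article, Randomization and Blindness: the method is stratified block randomisation, and "Participants will be stratified according to age". No other stratification factor is named. "The age stratification is divided into five categories, which are 2–3 years old, 4–5 years old, 6–7 years old, 8–12 years old", with a fifth stratum for children over 12. Random numbers come from a central platform and are "competitively selected by each clinical subcenter", so centre is not a stratum, although ten hospitals take part (Study Design).

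Protocol article, Statistical Analysis: the primary outcome is analysed by ANCOVA, and the terms are named: "The group is taken as a fixed effect, and the baseline value of the cough symptom score is taken as covariance into the model". The resulting two-sided 95% interval is compared with the non-inferiority margin. Age appears in the stated analysis only as a subgroup factor in three bands (2–3, 4–7 and 8–14 years), which merge four of the five strata into two.

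Table 5 of the same section lists the secondary outcomes. Against "Time-lapse analysis of measured value and changed value of cough symptom score" it sets "T test is used to compare the differences between groups". The cells below are blank. Read as carried down, the same test applies to the symptom-score AUC, onset of cough relief and clinical recovery time.

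**The concern.** Stratified randomisation balances age between the arms and so reduces the true variability of the treatment difference. An analysis gets the benefit only if its model contains the strata. If they are left out, the model standard error still includes the between-stratum variance and overstates the uncertainty.

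Here the design itself treats age as important. The cut-points of the five strata are those of the two dosing tables in Table 1 combined, so stratum is also a marker of dose band. The interval from this model alone decides whether a 0.5-day disadvantage is excluded, so needless width costs power on the main conclusion.

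The primary model is spelled out term by term, so this is not a detail left to a fuller document. A later plan that included age would be departing from the published model.

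The t tests raise a smaller, related point. The baseline cough score is collected and is a covariate for the primary outcome, but it is not a covariate for the later cough scores or the AUC.

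**Working it through.** **Inputs from Sample Size Calculation.** SD 2 days, true difference 0, margin 0.5 days, one-sided α 0.025, power 0.95, 417 evaluable per arm. R², the share of outcome variance explained by age stratum beyond baseline score, is not given. Values of 0.05 and 0.10 are assumed, with 0 and 0.20 as extremes.

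**Step 1: reproduce the plan's figure.** n = 2 × SD² × (1.960 + 1.645)² / margin² = 2 × 4 × 12.995 / 0.25 = 415.8, so 416 per arm. The exact noncentral-t version gives 417, with power 0.9501. The stated 417 is reproduced. It uses the full SD of 2, so the plan takes no credit for covariates.

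**Step 2: precision with and without age.** SE = 2 × √(1 − R²) × √(2/417). Half-width = 1.96 × SE. Power = Φ(0.5/SE − 1.96).

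| R² | SE | Half-width (days) | Power | n per arm for 95% power |
|---|---|---|---|---|
| 0 (age left out) | 0.1385 | 0.271 | 95.1% | 416 |
| 0.05 | 0.1350 | 0.265 | 95.9% | 396 |
| 0.10 | 0.1314 | 0.258 | 96.8% | 375 |
| 0.20 | 0.1239 | 0.243 | 98.1% | 333 |

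The SE without the stratum is too large by the factor 1/√(1 − R²): 1.026 at R² 0.05 and 1.054 at R² 0.10. In sample-size terms that is 416 − 396 = 20 and 416 − 375 = 41 children per arm. At 500 per arm, power is 97.7% without age, against 98.2% (R² 0.05) and 98.6% (R² 0.10).

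**Step 3: allow for the balance that stratification already gives.** Even when the model omits age, the estimate itself varies with the smaller SE; only the reported SE is too large. Power without age is then Φ((0.5 − 0.2715)/SE).
- R² 0.05: 0.2285/0.1350 = 1.693, or 95.5%, against 95.9% with age.
- R² 0.10: 0.2285/0.1314 = 1.739, or 95.9%, against 96.8% with age.

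So the loss actually suffered is about half of what the table in step 2 suggests. One-sided error at the margin is Φ(−1.96/√(1 − R²)): 0.022 at R² 0.05, 0.019 at 0.10 and 0.014 at 0.20, all below 0.025.

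**Step 4: simulation.** Five equally likely strata, blocks of four (assumed), 834 children, 4,000 runs per setting. The Monte Carlo error on 0.025 is √(0.025 × 0.975/4000) = 0.0025.

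| R² | Type I error without / with age | Power without / with age |
|---|---|---|
| 0 | 0.026 / 0.026 | 94.9% / 94.8% |
| 0.05 | 0.021 / 0.023 | 94.7% / 95.2% |
| 0.10 | 0.023 / 0.027 | 95.7% / 96.3% |
| 0.20 | 0.014 / 0.027 | 97.0% / 98.1% |

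The differences at R² 0.05 and 0.10 are close to simulation noise. The one at 0.20 is clear. The direction agrees with step 3.

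**Step 5: cough-score t tests.** Let r be the within-arm correlation of baseline and follow-up score, and k the ratio of baseline SD to follow-up SD. Relative to ANCOVA, the variance is 1/(1 − r²) for the measured value and (1 + k² − 2rk)/(1 − r²) for the change. Neither r nor k is in the documents.

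| r | k | Measured value | Change |
|---|---|---|---|
| 0.5 | 1 | 1/0.75 = 1.33 | 1/0.75 = 1.33 |
| 0.5 | 0.5 | 1.33 | 0.75/0.75 = 1.00 |
| 0.3 | 1 | 1/0.91 = 1.10 | 1.40/0.91 = 1.54 |
| 0.3 | 0.5 | 1.10 | 0.95/0.91 = 1.04 |

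Entry requires a day-plus-night score of at least 4 (Inclusion Criteria) on a scale that ends at 6 (Table 3). Baseline can therefore be only 4, 5 or 6, whereas follow-up can range from 0 to 6. A k below 1 is likely and r may be low. ANCOVA is never appreciably worse than either t test, but its advantage cannot be fixed from the documents.

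**The case against.** The strongest reply is that nothing invalid happens. Omitting a stratification factor makes the test conservative, the sample size was set with the unadjusted SD, and the trial keeps about 95% power or more on its own inputs. Unadjusted t tests are also valid in a randomised trial of this size. All of that stands and limits the weight of the point. It does not remove the mismatch between how children are allocated and how they are analysed, which costs nothing to repair.

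Four stronger readings are tempting, and the documents do not support them.
- *That the result could be biased or non-inferiority falsely claimed.* The error runs the other way.
- *That omitting centre is the same fault.* Centre is not a stratum, so its omission is only a possible precision point. The limitation in the Discussion about hospitals differing concerns testing machines and testing standards; it is not evidence of a centre effect on cough, which is scored on diary cards.
- *That the t tests disregard baseline altogether.* The change value of the cough score subtracts it. What is missing is covariate adjustment.
- *That the t tests waste a third more variance, or about 250 of 1,000 children.* That figure needs r = 0.5 and, for the change score, equal SDs at baseline and follow-up; the second is doubtful given the entry restriction.

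**Conclusion.** The point holds as a modest, conservative loss of efficiency. If age explains 5% to 10% of the outcome variance, the primary standard error is 2.6% to 5.4% too large and the half-width is 0.271 days instead of 0.265 to 0.258. By the sample-size formula, power at 417 per arm is 95.1% instead of 95.9% to 96.8%. Once the balance from stratification is counted, the shortfall is roughly 0.5 to 0.9 of a percentage point. If age is not prognostic there is no loss. These sizes rest on the assumed R². The omission itself is certain, because the model terms are stated. For the cough score and AUC the direction of the gain from baseline adjustment is clear but its size is unknown.

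**What to change.** Add the five-level randomisation age stratum as a fixed factor to the primary ANCOVA, alongside group and baseline cough score. Use the five strata as randomised, not the three subgroup bands.

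Analyse the cough score and the symptom-score AUC by ANCOVA with the corresponding baseline score and age stratum in place of the t tests. For the cough score, one such model replaces the separate tests of measured and changed values, because both give the same adjusted treatment effect.

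Centre may be added, fixed or random, as an option. Age-stratified CMH tests for the rates are a matter of preference; the planned χ² and Fisher tests are not in error.

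The cost is a wording change made before unblinding, plus four degrees of freedom for the age factor. No new data are needed and the sample size can stay as it is.

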#### Inclusion Criteria

(1) Participants with AB under the diagnostic criteria of Western medicine.(2) Those who meet the TCM diagnostic criteria of phlegm-heat stasis in lungs.(3) Participants aged 2–14 years.(4) Cough (day + night) score ≥4 points.(5) Duration of disease ≤48 h, no antibiotics, antitussives, phlegm-reducing drugs, and other Chinese or Western medicine that influence cough has been used before treatment.(6) The informed consent process complies with the regulations, and the legal representative and/or the child (≥8 years old) signs the informed consent.

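### The primary ANCOVA is valid but does not use time since illness onset, which must be judged for every child at entry; adding it is a cheap, optional gain in precision

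*Protocol article*

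**What the plan says.** In the protocol article, Statistical Analysis sets out an analysis of covariance for cough disappearance time. Group is the fixed effect and "the baseline value of the cough symptom score is taken as covariance into the model for analysis". No other covariate is named there.

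Two inclusion criteria bear on this:

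- Criterion 4 requires "Cough (day + night) score ≥4 points". Table 3 scores daytime and night cough from 0 to 3 each, so the total cannot exceed 6, and an eligible child scores 4, 5 or 6.
- Criterion 5 requires "Duration of disease ≤48 h". Someone has to judge time since onset for each child before randomization.

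The article does not say that the hours since onset are kept as a number. It also gives no figure for how strongly either variable predicts time to cough disappearance.

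Sample Size Calculation takes "the disappearance time of cough in the experimental group and the control group is about 5 ± 2 days", sets "The non-inferiority threshold of this study is set as 0.5 days, unilateral α = 0.025, power = 0.95", and concludes that "417 cases are needed for each group". This is raised to 500 per arm for withdrawals.

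**The concern.** The trial has already chosen to adjust its primary comparison for a baseline variable. The one it names has three possible values at entry. A second pre-randomization variable, measured on the same time scale as the outcome, is admitted over a 2-day range and not used. A child who has coughed for 40 hours at entry may be nearer the end of the illness than one who has coughed for 4 hours. If so, part of the spread in the outcome is predictable before treatment starts.

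Non-inferiority is decided by a confidence limit set against 0.5 days, so predictable variance left in the error term makes that interval slightly wider than it needs to be. The adjustment is credible only if it is named in advance: a covariate added after unblinding would look chosen from the data. What is at stake is some precision, not the validity of the test.

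**Working it through.** **Inputs from the protocol article.** Margin 0.5 days, SD 2 days, true difference 0, one-sided α 0.025, power 0.95, 417 per arm, 500 after the withdrawal allowance (Sample Size Calculation); onset 0-48 h, that is 0-2 days (inclusion criterion 5).

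**Assumptions, not in the documents.** Onset times are uniform over 0-2 days, so SD = 2/√12 = 0.577 day. Each extra day of prior illness shortens the remaining cough by b days, with b between 0 and 1. At b = 1, the illness runs its course regardless of when the child enters.

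**Step 1: the plan's own figure.** n = 2 × (1.960 + 1.645)² × 2² / 0.5² = 416 per arm by the normal approximation. The noncentral t gives 417, with power 0.9501. The stated 417 is reproduced. It uses the full SD of 2 days and takes no credit for any covariate.

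**Step 2: variance explained by onset time.** R² = (b × 0.577)² / 4. The residual SD is 2√(1 − R²), and the 95% CI half-width at 417 per arm is 1.96 × residual SD × √(2/417). Power is by the normal approximation.

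| b (day per day) | R² | n per arm for 95% power | Power at 417 | CI half-width at 417 (days) |
|---|---|---|---|---|
| 0 | 0% | 416 | 95.05% | 0.271 |
| 0.25 | 0.5% | 414 | 95.15% | 0.271 |
| 0.5 | 2.1% | 408 | 95.4% | 0.269 |
| 1 | 8.3% | 382 | 96.5% | 0.260 |

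At b = 1 the half-width falls by 0.271 − 0.260 = about 0.01 day. With all 500 per arm analysed, power would go from 97.7% to 98.5% at b = 1.

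**Step 3: chance imbalance.** The difference between arms in mean onset time has standard error 0.577 × √(2/417) = 0.040 day. At b = 1, its 95% range shifts the treatment difference by ±1.96 × 0.040 = ±0.078 day; at b = 0.5, by ±0.039 day. This does not come on top of the confidence interval. The unadjusted standard error is 2 × √(2/417) = 0.1385 day, and 0.040² / 0.1385² = 8.3%, the same share of variance as in Step 2. The interval already contains it.

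**Step 4: validity.** In 20,000 simulated trials at b = 1 and 417 per arm, one-sided type I error at the margin was 0.0240 without onset time and 0.0248 with it. Power was 95.2% and 96.7%. The simulation did not include the baseline cough score. If that score and onset time overlap, the extra gain from onset time would be smaller.

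**Step 5: an extreme case.** If half the children entered at 0 h and half at 48 h (SD 1 day) with b = 1, R² would be 25% and power at 417 would be 98.6%. This is the widest spread that criterion 5 allows, and it is not a realistic expectation.

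**The case against.** The strongest reply is that nothing in the plan is wrong. In a randomized comparison of means, omitting a prognostic covariate leaves the estimate unbiased and the test at its nominal level. The trial was sized on the full SD, so the variance tied to onset time is already paid for. The choice of prognostic variable is partly a matter of preference, the size of the gain rests on an assumed slope, and the SAP, which is not shown, may add covariates. All of that stands.

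A reader might infer more from the same facts, and the documents do not support these readings:

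- *Imbalance in onset time enters the estimate unprotected.* Step 3 shows that it is already inside the interval compared with the margin.
- *A 2-day spread in illness stage is four times the margin, so the comparison is compromised.* The 2 days is a difference between two children; the margin of 0.5 days applies to a difference between two means. They are not comparable.
- *A score confined to 4-6 can explain little.* The article gives nothing to show this. If scores were spread evenly over 4, 5 and 6 (an assumption), their SD would be √(2/3) = 0.82, and a slope of 0.71 day per point would explain (0.71 × 0.82)² / 4, or about 8%, as much as onset time at b = 1. A narrow range limits what the score can explain but does not make it a poor covariate.

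It is also fair to say that criterion 5 is a threshold check. Hours since onset are not shown to exist as data, and imprecise recall would shrink even the modest gains above.

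The objection does not remove the case for using a baseline quantity that the trial must assess anyway, at almost no cost and with no loss of validity.

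**Conclusion.** This is an optional precision improvement, not an error in the plan. The stated ANCOVA is valid, and its 95% power at 417 per arm does not rely on adjusting for onset time. Under uniform onset over 0-48 h and a slope of 0 to 1 day per day, adjustment explains 0-8.3% of the variance. At the top of that range it adds about 1.5 percentage points of power at 417 per arm, worth about 35 children per arm (417 − 382). At a slope of 0 it adds nothing. The factual basis is firm: a three-valued covariate at entry, and an onset time that must be judged but is not named in the model. The size of the benefit is an assumption throughout.

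**What to change.** In Statistical Analysis, prespecify before unblinding that the primary ANCOVA includes time from illness onset to randomization or first dose, in hours and as a continuous variable, beside the baseline cough score. On the CRF, record the hours as a number and not only as a yes/no check of criterion 5. If the SAP or CRF already does this, no change is needed.

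The cost is one sentence, one CRF field and one degree of freedom out of about 1000, with no additional children or visits. The downside is little or no gain if onset is poorly recalled or turns out not to be prognostic.
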